### Study Setting

A total of 400 Malaysian older adults aged 60 years and above will be recruited from the Klang Valley area. All physical activity interventions (with the exception of the forest walk and city walk) will be carried out in person within the compounds of Sunway University, whereas the cognitive stimulation interventions will be conducted online.

### Inclusion Criteria

The inclusion criteria are (1) healthy status (including those seeking regular medical attention); (2) some form of mobility (ability to walk short distances for at least 3 m); and (3) ability to communicate in at least one of the following languages: English, Malay, Mandarin, or Tamil.

### Exclusion Criteria

The exclusion criteria are (1) history of stroke, (2) diagnosis of a neurodegenerative disease (such as Alzheimer disease or Parkinson disease), (3) diagnosis of psychiatric disorders and/or being currently on psychiatric medications, (4) uncorrected auditory and/or visual impairments, (5) immobility or requirement for full-time caregiver assistance, (6) comprehension impediments or a Montreal Cognitive Assessment (MoCA) [29] score of less than 13.

Although the suggested cutoff score for the MoCA is 26, this might not be a true reflection of mild cognitive impairment in every country; hence, modifications to the cutoff score can be made according to the cultural and educational backgrounds of individuals in a particular country [30]. A systematic review of studies that used the MoCA in Southeast Asia reported that, in countries such as Malaysia, Singapore, China, and Taiwan, researchers used a cutoff ranging from 13 to 26 to take the educational background in these regions into account [31].

### Recruitment

Recruitment of participants will be conducted by advertising on social media, as well as visiting community clubs and meeting with community leaders in different housing areas across different socioeconomic strata. We refer to this cohort as the MyAgeWell cohort.

### Ethical Considerations

Ethics approval has been obtained from the Sunway University Institutional Review Board (reference SUREC2020/039; approval date: April 3, 2020). No substantive ethical issues have been identified with the conduct of our study. The protocol has also been registered on ClinicalTrials.gov with registration number NCT06376656 [32]. Participants will receive compensation for their participation in baseline assessments, interim measurements, and intervention sessions.

Participants will be recruited after providing written informed consent. Participants will retain the right to voluntarily withdraw from the study at any time. Unique codes will be assigned to each participant to ensure confidentiality. Records will only be accessible to involved researchers. Research findings from this study will be disseminated through presentations at conferences and publications in peer-reviewed academic journals.

### Baseline Measurements

The MoCA scores obtained by participants during their recruitment will serve as their baseline cognitive scores. In addition, cognitive behavioral measurements (2-back memory task [33], Wisconsin card sorting task [34,35], Tower of London task [36], and go/no-go task [37]), an electroencephalogram (EEG; resting state and during the go/no-go task), structural MRI, the everyday problem-solving task [38], and the Iowa gambling task [39] will be administered at baseline.

Participants will also answer a baseline questionnaire with regard to their demographics (gender, age, ethnicity, religion, spoken languages, marital status, occupation, educational level, savings, debts, assets, and social activities), health conditions (extracted questions from the Mini Nutritional Assessment [40] and Pittsburgh Sleep Quality Index [41] and voluntary disclosure of medical conditions), physical activity status (International Physical Activity Questionnaire) [42], mental health status (selected questions from the Center for Epidemiologic Studies Depression Scale [43] and State-Trait Anxiety Inventory [44]), Satisfaction With Life Scale [45], and life-course socioeconomic status (childhood, adulthood, and late adulthood). Participants may choose not to answer specific questions. In addition, saliva samples will be collected.

### Intervention

The intervention phase is intended to take place over a 4-year span, with interim measurements collected every 6 months. To maintain participant engagement, the intervention phase will be split into sequential activities, each carried out for a duration of 6 months.

#### Intervention Group 1: Cognitive Stimulation

The cognitive stimulation intervention will comprise psychoeducation, video gaming, jigsaw puzzle solving, and new language learning. These activities target multiple domains of cognition (eg, memory, attention, and executive function) and are both stimulating and practical to maximize ecological validity and adherence. For 6 months, participants will attend a weekly hour-long session of one of the aforementioned activities. Every 6 months, the participants in the cognitive stimulation group will alternate among the 4 above-mentioned cognitive stimulation activities until the end of the 4-year intervention period.

#### Intervention Group 2: Physical Activity

The physical activity intervention will comprise walking, dancing (Zumba), resistance training, and qigong sessions. These physical activity interventions are age appropriate and ecologically sound, with the potential to be adopted as part of participants’ healthy aging practices. For 6 months, participants will attend a weekly hour-long session of one of the aforementioned activities. Every 6 months, the participants in the physical activity group will alternate among the 4 above-mentioned physical activities until the end of the 4-year intervention period.

#### Intervention Group 3: Combined Cognitive Stimulation and Physical Activity

Participants in the combined cognitive stimulation and physical activity group will attend 2 sessions of interventions per week (a session of cognitive stimulation and a session of physical activity).

#### Control Group

Participants in the passive control group will not attend any intervention sessions but will attend the interim sessions every 6 months.

#### Record of Attendance

Attendance to each intervention session will be recorded, and participants will be asked to submit a weekly Google Form to record details of activities they have done over the previous week in their free time, which include physical, cognitive, social, and leisure activities not part of the intervention. This will be helpful for us to observe and control the frequency of other nonintervention activities while participants take part in the intervention.

#### Interim Measurements

Throughout the intervention period, participation in intervention components will be assessed via both self-reports and interviewer-administered surveys. The MoCA, cognitive behavioral measurements, EEG, and saliva collection will be repeated every 6 months.

#### End of Intervention Period

The MoCA, cognitive behavioral measurements, EEG, and saliva collection will be repeated at the end of the intervention period. MRI will only be performed during the last interim period (after 4 years) for all participants. A summary is provided in Figure 2.

**Figure 2 figure2:**
[figure not shown]
Interventions and data collection. EEG: electroencephalogram; MRI: magnetic resonance imaging.

### Sample Size

Simulation-based power analysis was performed using the *superpower* R package [46] in RStudio (version 2023.06.1; Posit PBC). This analysis determined that a sample size of 80 participants per intervention group would be sufficient to detect a medium effect size (η^2^_p_=0.06) in a 2 × 2 mixed-design interaction with 86.6% power. The 2 × 2 design was chosen as a comparison of pre- and postintervention measures between an intervention and control group, providing a basic assessment of whether a specific intervention is effective. This assumes a correlation of at least 0.8 between repeated measures. We calculated that a sample of 400 would be necessary to reach our goals, given that we expect an attrition rate of 20% (80/400 participants) between the pre- and postintervention phases for several reasons (ie, death, decline in health, and dropouts in training sessions).

### Data Collection

#### Overview

A copy of a personal information sheet and a consent form will be given to participants to inform them about the study and obtain consent. Participants will answer a baseline questionnaire using a Google Form. A researcher will help administer the MoCA to the participants based on their preference (online or in-person session). Structural MRI will be used to determine brain structure (gray matter volume), and EEG will be used to determine brain function (electrophysiological activity), both while participants are at rest and while they complete a cognitive task (the go/no-go task). After a brief rest, participants will be asked to rinse their mouths with water to proceed with saliva collection. They will then be seated comfortably and asked to lean forward and not swallow. After 5 minutes, saliva will be collected in a collection tube via passive drooling [47].

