## Methods

### Trial Design

This quasi-randomized controlled trial has a longitudinal mixed-subject design for a total of 4 years (between-subject: intervention type; within-subject: repeated measures on various tasks and assessments). Participants will be quasi-randomly allocated to 1 of the 4 groups (cognitive stimulation, physical activity, combined cognitive stimulation and physical activity, and control) in a sequential cycle by experimenters to ensure balance in group sizes. Minor adjustments may be made for a small proportion of participants (anticipated to be fewer than 15% of the intervention sample) to accommodate logistical feasibility, such as availability during intervention sessions or access to required resources (eg, internet-enabled devices for online cognitive sessions). These adjustments will be applied only when necessary. Participants and experimenters will not be blinded to group assignment. Participants will be tested at baseline and every 6 months until the end of 4 years. Structural magnetic resonance imaging (MRI) will only be performed at baseline and at the end of the intervention period.

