#### EEG Measurement

EEG data are acquired using a portable multichannel EEG system with dry electrodes arranged according to the International 10-20 system, allowing for coverage of the frontal, central, parietal, temporal, and occipital regions. This configuration is suitable for assessing large-scale cortical activity associated with executive control, attention, and response inhibition. EEG signals are sampled at a temporal resolution of 500 Hz, allowing for reliable characterization of both oscillatory activity and task-related event-related potentials (ERPs) in accordance with manufacturer specifications. Resting-state EEG is recorded for a total of 4 minutes under counterbalanced eyes-open and eyes-closed conditions segmented into 1-minute blocks to minimize fatigue and habituation effects. Participants are instructed to remain relaxed and awake and avoid goal-directed cognitive activity during recording.

EEG preprocessing includes band-pass filtering using standard frequency ranges for resting-state and task-based analyses, as well as artifact handling procedures comprising visual inspection and removal of segments contaminated due to eye blinks, muscle activity, movement, or electrode instability. Sessions with excessive artifacts are documented and excluded as appropriate to ensure data quality. During the go/no-go task, EEG is recorded concurrently with behavioral performance. Task-related analyses focus on ERPs associated with response inhibition and cognitive control, specifically, components time-locked to stimulus presentation during go and no-go trials. ERP waveforms are derived by averaging across trials after artifact rejection, with component amplitudes and latencies extracted from fronto-central electrode sites commonly implicated in inhibitory control processes. Longitudinal EEG changes are examined at 6-month intervals using mixed-effects modeling, which accommodates repeated measurements, missing data, and interindividual variability. This analytic approach enables the examination of within-subject changes over time while accounting for relevant covariates, thereby providing sensitive indexes of functional neural adaptation associated with the interventions.

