## Results

From the perspective of psychology, primary outcomes will be the changes in cognitive scores (MoCA), cognitive behavioral measurements, everyday problem-solving, and Iowa gambling tasks. From the perspective of neuroscience, primary outcomes will be the changes in EEG and MRI. From the perspective of economics, the primary outcome will be the cost-benefit analysis of the intervention. From the perspective of biology, primary outcomes will be the changes in salivary biomarkers (lactoferrin, CRP, and telomere length).

The study grant was awarded in August 2019. Participant recruitment was delayed due to the COVID-19 pandemic, as the target population comprised healthy older adults who were particularly vulnerable during periods of movement restrictions and heightened infection risk. Recruitment commenced in May 2022 and was completed in July 2023. A total of 400 healthy older adults were successfully enrolled. The intervention phase began in 2023 and is currently ongoing, with participants undergoing intervention activities and follow-up assessments at 6-month intervals throughout the study period. At the time of manuscript submission, follow-up data collection and data analysis are ongoing. Baseline characteristics and cross-sectional findings from the cohort have been reported separately, while analyses of intervention-related outcomes are currently underway. The first intervention outcome publications are anticipated from 2026 onwards as follow-up assessments are completed, and additional longitudinal data are available for analysis.

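### MoCA mode follows participant preference and is not held constant within participant, so mode changes could differ by arm; masking of MoCA scoring and EEG cleaning is not stated

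*Protocol article*

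**What the plan says.** The Overview under Data Collection gives the only rule on how the MoCA is delivered: "A researcher will help administer the MoCA to the participants based on their preference (online or in-person session". It names no time point for that preference.

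The MoCA is both baseline and repeated outcome. Under Baseline Measurements, "The MoCA scores obtained by participants during their recruitment will serve as their baseline cognitive scores". Under Interim Measurements, "The MoCA, cognitive behavioral measurements, EEG, and saliva collection will be repeated every 6 months". The Results section lists it first among the psychology outcomes: "primary outcomes will be the changes in cognitive scores (MoCA), cognitive behavioral measurements, everyday problem-solving, and Iowa gambling tasks".

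On the arms, Study Setting says that "the cognitive stimulation interventions will be conducted online", while physical sessions are mostly on campus. The combined arm has both kinds of session and the control arm has only the interim sessions. Trial Design lets allocation depart from the sequential cycle for practical reasons, one being access to an internet-enabled device. This is anticipated for fewer than 15% of the intervention sample.

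On blinding, Trial Design says: "Participants and experimenters will not be blinded to group assignment". EEG Measurement describes "artifact handling procedures comprising visual inspection and removal of segments contaminated due to eye blinks, muscle activity, movement, or electrode instability" and lets sessions with too many artifacts be dropped, with no threshold given. It does not say who does this work. Statistical Methods names age and sex as examples of covariates and does not mention MoCA mode.

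**The concern.** If an online and an in-person MoCA differ systematically in score, a participant who changes mode between baseline and follow-up shows a change that is not cognitive. If such changes are equally common in all arms they cancel in the comparison. If not, they enter the arm-by-time contrast, which is the effect the trial is designed to estimate. More participants would not reduce this bias, and it can be assessed only where mode has been recorded.

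The arms differ in ways that make unequal mode change plausible: online sessions in two arms, campus attendance in two, neither in the control arm, and an allocation adjustment tied to internet devices. In addition, MoCA scoring and the rejection of EEG segments by eye both involve judgement, and the article mentions no masking for either.

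**Working it through.** **1. The planned effect, as a yardstick.** Inputs from Sample Size: 80 per group, partial eta squared 0.06, correlation 0.8, stated power 86.6%, attrition 20%. Alpha 0.05 is from Statistical Methods.

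- f² = 0.06 / 0.94 = 0.0638; denominator df = 160 − 2 = 158; λ = 0.0638 × 158 = 10.09.
- Power from the noncentral F(1, 158) is 88.4%, which is 1.8 points above the stated 86.6%. The stated value comes from simulation. With 1,000 runs (an assumption; the number is not given) the 95% Monte Carlo margin would be about ±2.1 points, so the figure is reproduced.
- Enrolment: 4 × 80 = 320, and 320 / 0.80 = 400, as stated.
- Effect in SD of change: √(10.09 / 40) = 0.502. The SD of change is √(2 × (1 − 0.8)) = 0.632 raw SD. The planned effect is 0.502 × 0.632 ≈ 0.32 raw SD.

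**2. The bias.** Let m be the mode effect (online minus in person, in raw SD, assumed equal in all arms). Let Δ be an arm's online share at follow-up minus its online share at baseline. Then

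bias in the arm-by-time contrast = m × (Δ in arm A − Δ in arm B).

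The driver is the difference in mode *change*. A difference in online share that stays constant from baseline to follow-up drops out. If every participant keeps one mode, Δ = 0 in every arm and the bias is zero.

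**3. Size on assumed values.** The documents give neither m nor the shares. The type I error uses λ = (bias / 0.632)² × 40 with 80 per group; for bias 0.08, λ = 0.64.

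| Mode effect (SD) | Difference in mode change | Bias (SD) | Share of 0.32 SD | Type I error (nominal 5%) |
|---|---|---|---|---|
| 0.1 | 10 points | 0.01 | 3% | 5.1% |
| 0.2 | 20 points | 0.04 | 13% | 6.8% |
| 0.2 | 40 points | 0.08 | 25% | 12.5% |
| 0.3 | 40 points | 0.12 | 38% | 22.2% |

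**4. How mode change could differ by arm.** There are two routes.

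- *Follow-up MoCA in person for everyone*, because EEG and saliva are collected at the same visits. Anyone tested online at recruitment then switches, and an arm's Δ is minus its baseline online share. Sequential allocation should roughly balance that share. Moving people without devices away from the two arms with online sessions could unbalance it.
- *Online MoCA still offered at follow-up.* Preference is then expressed after allocation, and weekly online sessions in two arms may shift it.

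**5. Masking.** Trial Design states that participants and experimenters are unblinded. The MoCA is administered with a researcher's help. EEG segments are removed by eye. No section names a masked assessor, scorer or EEG reader. Unique participant codes already exist (Ethical Considerations), so masked files are feasible.

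**The case against.** The strongest reply is that the mode sentence directly follows consent and the baseline questionnaire, and that the MoCA is also a screening test with an exclusion below 13. Preference may therefore be asked once, before allocation, where it cannot respond to arm. All arms, controls included, attend interim sessions with EEG and saliva collection, so follow-up MoCAs may be in person throughout. The combined arm trains online and also comes to campus, so the arms do not split cleanly into online and in-person groups. All of this stands and limits drift in preference. It does not remove the concern: in-person follow-up is itself a switch for anyone tested online at recruitment, and nothing in the article limits preference to baseline or fixes mode afterwards.

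Two stronger readings are tempting. A reader might infer that participants choose mode afresh at every test; the Overview gives no time point. A reader might also infer that EEG is cleaned by staff who know the arm; EEG Measurement names no reader, Trial Design speaks only of participants and experimenters, and Data Management mentions data coders separately. Masking of offline processing is also a detail that an article may leave to the full protocol. The masking part is therefore a point to state and secure, and the article does not show it to be a defect.

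Finally, mode at follow-up is chosen or imposed after allocation. Adjusting for it, or restricting to those who kept one mode, conditions on a post-allocation variable and can create bias of its own. That is correct and confines such analyses to a sensitivity role.

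**Conclusion.** The point holds in a limited form. The article states a rule for a repeated primary outcome, participant preference, that permits mode to change between baseline and follow-up, and it contains no safeguard against this happening unequally by arm. It also states that experimenters are unblinded and does not state masking for MoCA scoring or for visual EEG rejection and session exclusion.

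The size of any bias is unknown. A mode effect of 0.2 SD with a 20 to 40 point difference in mode change would give 0.04 to 0.08 SD, 13% to 25% of the planned effect. Both factors are assumptions, and with 0.1 SD and 10 points the bias is negligible. The documents do not support saying that arm-related measurement error has occurred, or that mode goes unrecorded. The correction is worth making because it is cheap and follow-up is still under way.

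**What to change.** - Replace free preference with one mode per participant for all remaining MoCA assessments, matching the baseline mode where feasible. The primary model compares baseline with the post-intervention time point, so the match matters most at the final assessment.
- Record mode for every past and future MoCA.
- Keep the primary model as planned. Add two sensitivity analyses, one adjusting for mode and one restricted to participants with constant mode, and note in both that mode is a post-allocation variable.
- Where existing staffing allows, have the MoCA given by researchers who do not run that participant's sessions.
- Clean EEG on files carrying only the existing participant codes, without arm labels, until segment and session exclusions are locked. State this in the plan.

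Cost: participants lose free choice of mode, and there is minor scheduling and file-handling work. No new participants and no change to the interventions are needed.

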#### Structural MRI

Structural MRI data will be acquired using a 3.0-Tesla scanner. High-resolution T1-weighted images will be obtained for gray matter assessment, with isotropic voxel resolution suitable for voxel-based morphometry (eg, 1 × 1 × 1 mm^3^). Preprocessing will include quality inspection, tissue segmentation, spatial normalization, and smoothing. Gray matter volume will be quantified via voxel-based morphometry, with longitudinal analyses conducted after the intervention using general linear models adjusting for covariates (age, sex, and intracranial volume). These measures are interpreted as indexes of cumulative, longer-term neural adaptation.

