### Statistical Methods

The primary analysis will be conducted using a repeated-measure linear mixed-effects model with time (baseline vs postintervention time point) as a within-subject factor and intervention type (cognitive stimulation vs physical activity vs combined vs control) as a between-subject factor. Participants will be included as a random effect to account for repeated measurements. Analyses will follow the intention-to-treat (ITT) principle, with baseline covariates such as age and sex included as fixed effects where appropriate.

Missing data will be handled using both ITT and per-protocol approaches. For participants with minimal missing data (<15%), analyses will primarily follow ITT principles without imputation, as this level of missingness is unlikely to bias the results. If missing data exceed this threshold, appropriate imputation methods, such as multiple imputation, will be applied. Sensitivity analyses will also be conducted to ensure robustness across both ITT and per-protocol analyses.

For exploratory purposes, paired 2-tailed *t* tests may be conducted to compare outcome values (before and after the intervention for each intervention phase, eg, telomere length), and one-way ANOVA may be used for simple between-group comparisons at a single time point. Results with a *P* value of less than .05 will be considered statistically significant, with appropriate attention to multiple testing for secondary analyses.

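### The MRI model does not list baseline gray matter as a covariate, a modest loss of precision, and the stated multiplicity rule does not reach the primary MRI outcome

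*Protocol article*

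**What the plan says.** All references are to the protocol article.

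- Trial Design fixes two scans: "Structural magnetic resonance imaging (MRI) will only be performed at baseline and at the end of the intervention period".
- Structural MRI gives the measure, "Gray matter volume will be quantified via voxel-based morphometry", and the model, "longitudinal analyses conducted after the intervention using general linear models adjusting for covariates (age, sex, and intracranial volume". It does not say whether the response is the final scan or the change. It also does not say whether inference is voxelwise, regional or global.
- Results gives the outcome's status: "From the perspective of neuroscience, primary outcomes will be the changes in EEG and MRI".
- Statistical Methods describes the general primary model as a linear mixed model with "time (baseline vs postintervention time point) as a within-subject factor", and sets the significance rule: "Results with a *P* value of less than .05 will be considered statistically significant, with appropriate attention to multiple testing for secondary analyses".

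**The concern.** There are two separate issues.

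**Covariates.** With two scans per person, the best available predictor of the final gray matter volume is normally the same person's baseline volume. The covariate list is specific and does not contain it. Intracranial volume mainly captures head size, which explains differences between people and should explain little of the change within a person. A model built as listed is therefore less precise than the planned scans allow.

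**Multiplicity.** The significance rule places multiplicity control with secondary analyses, but MRI change is declared primary. Voxel-based morphometry can yield one total, several regional values or a whole map of tests. Unless the MRI result is a single number, following the rule as worded leaves the false-positive rate of a primary outcome above 5%. The article's Discussion expects imaging to show whether the interventions preserve brain structure, and this analysis would carry that claim.

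**Working it through.** **The plan's own figures.** The Sample Size section gives 80 per group, partial eta squared 0.06, a pre-post correlation of at least 0.8, 86.6% power for a 2 × 2 interaction, and 20% attrition.
- f² = 0.06/0.94 = 0.0638. Noncentral F with 1 and 158 df, alpha 0.05, noncentrality 0.0638 × 158 = 10.1: power 88.4%.
- With f = 0.25, noncentrality 0.0625 × 158 = 9.9: power 87.8%.
- Both lie within 2 points of 86.6%, which was itself obtained by simulation. The figure is reproduced.
- 4 × 80 = 320, and 320/0.8 = 400, as stated.

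**Precision.** Assume equal SD at both times, set to 1, and correlation r between scans. The article's 0.8 is generic, and it gives no r for gray matter. The error variance per person is:
- change score: 2(1−r)
- final scan adjusted for baseline: 1−r²
- ratio, adjusted to change: (1−r²)/[2(1−r)] = (1+r)/2

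The ratio is 0.75 at r = 0.5, 0.90 at r = 0.8, 0.95 at r = 0.9 and 0.99 at r = 0.98.

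**Power at r = 0.8, 80 completers per arm, two-sided 0.05.** Two-sided testing is stated only for the exploratory t tests and is assumed here. A noncentrality of 9.526 gives exactly 86.6%. This corresponds to a between-arm difference in change of √(9.526 × 2 × 0.4/80) = 0.309 SD. By normal approximation:
- change score: SE = √(2 × 0.40/80) = 0.100; 0.309/0.100 − 1.96 = 1.13; power 87.0%.
- baseline-adjusted: SE = √(2 × 0.36/80) = 0.0949; 0.309/0.0949 − 1.96 = 1.29; power 90.2%.
- Equivalent sample size: 80 × 0.90 = 72 per arm would give the change-score power.

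**Multiplicity.** For k independent tests each at .05, the chance of at least one false positive is 1 − 0.95^k:
- k = 1: 5%
- k = 3: 14.3%
- k = 10: 40.1%
- k = 59: 95.2%

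The article gives no k, so these values show a range. Regional volumes are likely to be positively correlated, which would lower the figures for k above 1. As a conditional check on voxelwise reading, 60 smooth null maps were simulated (8 mm smoothing and 3 mm voxels, both assumed). All 60 had at least one voxel below an uncorrected .05.

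**The case against.** **Precision.** A reader might infer that the model is fitted to final scans alone. Listing intracranial volume invites this, since that covariate is most useful for raw volumes. The loss would then be large: error variance 1/0.36 = 2.78 times the baseline-adjusted value at r = 0.8, and power near 50%. The article does not support this. It calls the MRI analysis longitudinal, schedules a baseline scan, defines the outcome as change, uses baseline against postintervention as a factor in its general primary model, and powers the trial on a pre-post interaction. What remains is a choice between change and baseline adjustment, both accepted methods. Allocation is quasi-random, with some participants moved for logistical reasons, so the two can also differ in bias if arms start unequal. That objection stands to this extent: the omission is an inefficiency and an ambiguity, not an error.

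**Multiplicity.** A reader might also infer that voxel maps will be read at an uncorrected .05, making false positives near certain. Spatial normalization and smoothing do point toward voxelwise comparison. However, the article states no voxel threshold, corrected or not, and whole-brain correction is a detail that an article may leave to the full plan. One could also argue that the MRI general linear model is not the primary mixed model and so counts among secondary analyses. These points rule out the near-certainty claim. They do not remove the mismatch, because the rule names secondary analyses only and the Results section calls MRI change primary. An analysis plan that follows both statements would inherit the gap.

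**Conclusion.** The point holds in a limited form.

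- Leaving out baseline gray matter costs about 10% of variance at r = 0.8 and 5% at r = 0.9, or about 3 points of power (87.0% against 90.2%) at r = 0.8. This assumes equal SDs, 80 completers per arm and a correlation that the article does not give for gray matter. At very high r the loss nearly vanishes.
- The significance rule, taken as written, provides no false-positive control for the primary MRI outcome. The size depends on an unstated number of tests: 5% for one global volume and about 40% for ten independent regional volumes. It approaches certainty only under uncorrected voxelwise inference, which is not stated.

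Both should be settled before the final scans are analyzed. On the article's dates (intervention from 2023, lasting 4 years), those scans fall from about 2027.

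**What to change.** **Structural MRI section.** State the response and how the baseline scan enters, by one of two routes:
- Model the final scan with baseline gray matter (same voxel, region or total) added to the listed covariates, and arm as the tested term.
- Put both scans in the linear mixed model of the Statistical Methods section, with time by arm as the tested term. This keeps people with only one scan, which matters with 20% attrition expected. With baseline means free to differ by arm, complete pairs contribute about the same precision as a change score, so the main gain of this route is retention.

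**Statistical Methods section.** Extend the multiplicity sentence to the primary MRI analysis, either by whole-brain family-wise or false-discovery correction or by naming one total gray matter volume as the confirmatory MRI outcome, with maps as supporting results.

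**Cost.** Wording and minor analysis work on scans already planned, and somewhat stricter thresholds for MRI findings. No new data are needed.
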